##### The Early Sociocognitive Battery of the Very Early Processing Skills [39, 40]

This assesses children’s sociocognitive skills (social responsiveness, joint attention and symbolic comprehension).

##### Repetitive Behaviours Questionnaire [41]

A 26-point parent questionnaire for assessing repetitive behaviours in children with ASD.

##### The Developmental Behaviour Checklist-Parent (2nd Edition; DBC-P) [42] Disruptive/Anti-social and Anxiety Subscales

A 96-item instrument used for the assessment of behavioural and emotional problems in young people aged 4–18 years with developmental and intellectual disabilities. It is completed by a parent or carer. In PACT-G we will use two subscales: the Disruptive/Anti-social and the Anxiety Subscale. This constitutes 36 items.

##### Strengths and Difficulties Questionnaire (SDQ) – Parent and Teacher versions

A 25-item brief measure of psychological wellbeing in 2–17 year olds (Goodman, 1997) [43]. In PACT-G, it will be completed by both parents and teachers.

##### Child Health Utility 9D [44] (CHU9D)

A paediatric measure of health-related quality of life. It consists of nine items, each responded to with one of five levels (ranging from no problems to severe problems). The CHU9D is designed to be completed by children aged 7–17 years. Proxy completion is also possible for younger/developmentally disabled children. In PACT-G parents will be asked to complete this questionnaire on behalf of their child.

##### Warwick and Edinburgh Mental-Wellbeing Scale [45]

Parent-rated wellbeing questionnaire recommended by UK Department of Health as the preferred measure of mental wellbeing important to incorporate in studies of this kind.

##### Tool to Measure Parental Self-efficacy [46]

A 48-item, self-report measure of parenting competence. It is a measure of possible change in parent’s confidence in their ability to make a difference to their child’s development. Completed at baseline and endpoint assessments.

##### Child and Adolescent Service Use Schedule (CA-SUS) [25] and School Service Use Schedule

Developed to record therapies and service use accessed throughout participation in the study. Forms were adapted to young populations with autism in our PACT and PACT 7–11 studies [6].

##### Working Alliance Inventory – Short Revised (WAI-SR) [47]

A measure of engagement with therapy for parents and learning support assistants in intervention group only. For parents and LSAs, there is a simple rewording of the client and therapist versions of the WAI-SR, which has been validated and is now frequently used. This will be completed at 2 and 5 months into the intervention.

##### Demographic, clinical and family language information

We will collect relevant demographic and clinical information and details of home language(s) spoken with the child.

### Procedures

#### Data collection

Research staff will confirm eligibility and obtain consent. Baseline assessment will be undertaken prior to treatment assignment. Randomisation will be done through the King’s Clinical Trials Unit web-based randomisation service. Allocation will be by stratified block randomisation, controlling for treatment centre, age strata (under fifth birthday, fifth birthday and older) and gender. Each case will be assigned a participant ID number and treatment allocation emailed separately to the treatment centre therapists.

The primary outcome and putative mechanisms are coded from videotape, by researchers at the other sites, trained to high levels of reliability and blinded to intervention allocation. A randomly selected proportion of assessments will be double rated for reliability. All other researcher assessments are also blinded; parent and teacher questionnaires/interview measures non-blinded. Participant families cannot be blinded to allocation.

All therapy sessions are videotaped. Variability due to therapist effects will be minimised by frequent clinical supervision and checks on continuing therapist fidelity against the treatment manual; randomly selected sessions for each therapist will be formally coded for fidelity over the course of the study by independent clinicians using the model successfully used in PACT.

Adverse events are enquired for by researchers at each contact with the family. Adverse events are also collected in parallel by trial therapists, as and when a situation becomes known to them, and documented separately. As well as recording adverse events in a pre-defined standard format, we include adverse events relating to child health, wellbeing and behaviour, significant issues at school, and family events such as separation or significant parental ill-health.

Extensive information-sharing and engagement activities with clinical teams and local mainstream and specialist schools will be undertaken to promote clinical referrals and engagement with both home and education aspects of the intervention. Regular trial newsletters to participating families, schools and nurseries and clinical teams, along with voucher payments to schools and nurseries will act to maintain involvement and adherence. Families receive an individualised feedback report on the assessments conducted with their child, copied to school and clinical teams if desired. A local referring clinician for each participant will be informed of study progress and findings, with procedures for clinical support and aftercare beyond the study should this be necessary.

#### Data management

All data in the trial will be anonymised. A central master file will be held by the trial manager at The University of Manchester. This will contain the key linking anonymised trial name to personal details. The main trial data will be entered into the web-based data entry service of King’s College Clinical Trials Unit, which has a full audit trail. Appropriate quality control will be carried out during the trial and before the database lock.

Primary analysis of the data will take place by the trial statisticians and chief investigator. Other members of the team will also have access to data within a publication protocol agreement, and will be able to undertake analysis as appropriate and necessary. This could include analysis of baseline data prior to primary endpoint analysis, and of outcome data but only after the primary analyses are completed. Any arrangements for other researchers in the general field to have access to the primary data will be negotiated separately and COREC informed.

## Statistical analysis

### Sample size calculations

The PACT trial showed an effect of ES 1.22 (0.85, 1.59) on parental synchrony (DCMA), which mediated 70% of the ES 0.41 (0.08, 0.74) on child communication, which in turn mediated 72% of the ES 0.24 (0.59, 0.11) on symptom outcome (ADOS). The intervention strategies in the PACT-G trial are specifically targeted to enhance generalisation of the child communication to increase effects on primary outcome in home, education and research settings. Therefore, we expect the ES for the symptom outcome to be substantially above 0.24 and clinically meaningful (see above). Power was calculated using the sampsi command in Stata for an analysis using analysis of covariance (ANCOVA) with alpha = .05, with pre and post measures correlated at .67 (based on PACT trial). With 110 cases followed up in each group (70/70 pre-school and 40/40 school-age) 80% power is retained for ES = 0.28 and 90% power for ES = 0.33. Allowing for 10% attrition (compared to 4% in PACT) we propose to recruit 244 families (~ 82/site − 52 pre + 30 school-age).

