### Settings

NHS clinics, homes, local schools with specialist autism units, and specialist autism school settings; in Greater Manchester, London and North-East England.

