#### Education-setting sessions

In most cases, therapy in the educational setting begins after the parent has commenced therapy at home. The start times and duration of education-based therapy are flexible to fit around the school-term schedule. In the education setting PACT-G sessions will be delivered to trained learning support assistants (LSA), who are staff with a specific remit to assist children with special educational needs to access the curriculum- and broader school-based activities, e.g. mealtimes, etc. LSAs and other education staff receive an initial training session to introduce them to PACT-G. The education-based intervention then consists of therapist-LSA sessions that mirror the therapist-parent sessions in the home. Videos are made of the LSA and the child and are used to coach the LSA in the use of PACT-G strategies in a similar procedure to the parent. The LSA then implements these with the child daily in class time. There are a maximum of 12 therapist-LSA sessions over 6 months, alternating in-school visits and Skype/telephone consultation. PACT-G strategies are expected to be integrated in a complementary way with other communication strategies that may already be in use in the school.

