#### Phase 1 – Efficacy analysis

We will test the primary hypothesis for between-group difference in the outcome ADOS total score using linear regression, stratified by ADOS module, covarying by baseline ADOS total score and dummy variables for site, gender and age group. Standard residual diagnostics will be applied and skew minimising transformations adopted where required. An overall effect size will be calculated pooling stratum specific estimates for strata defined by the ADOS module, weighted by their precision, using a 95% confidence interval estimated from 5000 bootstrap replicates.

The secondary outcomes will be analysed in a similar way but without stratification by ADOS module. A forest plot of effect sizes for primary and secondary outcomes will be presented. A test of homogeneity of effect size for the ADOS and BOSCC will be reported.

The primary paper will report a test of homogeneity of effect for the primary outcome in pre-school and school-age children. To be consistent with the treatment main effects analysis, the test of difference in treatment effect by age group will be based on the bootstrap *p* value over 5000 replicates of the pooled within-ADOS stratum estimate of the treatment difference. A secondary paper (see phase 3) will report an optimal moderation index [50] including bias correction from over-fitting to a finite sample.

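### The stated power assumes independent children, and the primary model has no therapist term, although PACT-G children are nested in therapists who see no TAU child

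*Protocol article*

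**What the plan says.** The section Sample size calculations of the protocol article bases power on Stata's sampsi for an "analysis of covariance (ANCOVA) with alpha = .05", a pre-post correlation of .67 taken from the earlier trial, and 110 children per group at follow-up. The result is given as "80% power is retained for ES = 0.28 and 90% power for ES = 0.33". No ICC, caseload or design effect accompanies it.

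The section Training and fidelity of treatment keeps trial therapists away from TAU families, so therapist caseloads exist in one arm only. The section Data collection acknowledges that therapists may differ and answers it by conduct: "Variability due to therapist effects will be minimised by frequent clinical supervision and checks on continuing therapist fidelity against the treatment manual".

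The section Phase 1 – Efficacy analysis names the primary model: linear regression within ADOS module, with baseline ADOS, site, gender and age group as covariates. The module-specific estimates are pooled by precision, "using a 95% confidence interval estimated from 5000 bootstrap replicates". There is no therapist term, and the unit of resampling is not stated. The section Analysis plan announces a separate SAP, which is not among the documents at hand.

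**The concern.** The design is partially nested: PACT-G children share therapists and TAU children have none. If therapists differ in the results they obtain, that variation enters one arm's mean and cannot cancel in the comparison. Site dummies do not absorb differences between therapists within a site. Supervision and fidelity checks may shrink the variation, but nothing in the article shows that they remove it.

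A calculation that ignores this variation overstates power, and a child-level standard error is too small. There is little slack. The sample size section itself cites 0.24 as the earlier trial's effect on the ADOS, which is below the 0.28 that the trial is powered to detect.

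**Working it through.** **Inputs from Sample size calculations.** Alpha 0.05 (taken as two-sided, which fits the stated figures), pre-post correlation 0.67, n = 110 per arm.

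**Inputs not in the article, assumed.** 6 to 12 therapists with equal caseloads of m = 110/k, that is 18.3 down to 9.2 analysed children each. ICC of 0.01 to 0.05 on the scale of the ANCOVA residual, in the PACT-G arm only.

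**Step 1: reproduce the stated power with independent children.**

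- Residual variance = 1 − 0.67² = 0.5511, so residual SD = 0.742.
- SE = √(0.5511 × 2/110) = 0.1001.
- Power at 0.28 = Φ(0.28/0.1001 − 1.96) = 79.9%.
- Power at 0.33 = Φ(0.33/0.1001 − 1.96) = 90.9%.
- Detectable effect size: (1.960 + 0.842) × 0.1001 = 0.280 at 80% power, and (1.960 + 1.282) × 0.1001 = 0.324 at 90%.

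Other independence-based calculations do not fit: one-sided gives 87.5% and 95.1%, change scores 72.4% and 85.4%, and no baseline covariate 54.6% and 68.7%. The stated figures are therefore a two-sided ANCOVA with no allowance for clustering. The 0.28 figure has no room to spare. The 0.33 figure has a little, because 90% is already reached at 0.324.

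**Step 2: add therapist nesting in the PACT-G arm only.**

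- Design effect in that arm: DE = 1 + (m − 1) × ICC.
- SE = √(0.5511 × (DE + 1)/110).
- True size of a nominal 5% test that ignores clustering = 2 × [1 − Φ(1.96 × 0.1001/SE)].

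Worst case in the range, 6 therapists and ICC 0.05: DE = 1 + 17.33 × 0.05 = 1.867; SE = √(0.5511 × 2.867/110) = 0.1198; power at 0.28 = Φ(2.336 − 1.96) = 64.7%.

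| Therapists | ICC | DE | Power at 0.28 | Power at 0.33 | ES at 80% power | Size if ignored |
|---|---|---|---|---|---|---|
| 12 | 0.01 | 1.08 | 78.3% | 89.8% | 0.286 | 5.5% |
| 12 | 0.05 | 1.41 | 72.2% | 85.2% | 0.308 | 7.4% |
| 9 | 0.01 | 1.11 | 77.7% | 89.4% | 0.288 | 5.6% |
| 9 | 0.05 | 1.56 | 69.6% | 83.0% | 0.317 | 8.3% |
| 6 | 0.01 | 1.17 | 76.5% | 88.5% | 0.292 | 6.0% |
| 6 | 0.05 | 1.87 | 64.7% | 78.6% | 0.336 | 10.2% |

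The size column applies when therapist effects vary around a mean of zero. The normal approximation ignores the few degrees of freedom that 6 to 12 therapists supply.

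**Step 3: check whether shared schools have the same consequence.** In a simulation, 220 children in schools of 2 or 4 were allocated individually to two equal arms, with a school ICC of 0.05 or 0.20 common to both arms (8000 runs per setting). The SD of the treatment difference was 0.099 to 0.100, against 0.100 under independence, and the type I error was 4.9% to 5.1%. There was no inflation.

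**The case against.** **The size is assumed throughout.** This stands. At the mild end (12 therapists, ICC 0.01), power is 78.3% and 89.8%, hardly different from the stated figures. The design also gives some reason to expect a small ICC: therapists coach parents and learning support assistants, and the ADOS is taken with a researcher and coded blind at another site. That is a reason to show a range, not to assume zero without saying so.

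**The type I error need not be inflated.** This stands in part. If the treatment does nothing for any child, individual randomisation keeps the test near 5%. Inflation needs therapists whose effects differ but average to nothing. Treating therapists as random is also a choice: it generalises beyond the therapists in this trial.

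**The SAP may deal with it.** It may, particularly for the resampling unit. A reader might infer that the final confidence interval is bound to be too narrow; the article does not support that. The power statement and the covariates of the primary model are nevertheless fixed in the article, and a SAP that follows them would carry the omission forward.

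**Schools.** Because the Settings section lists "local schools with specialist autism units, and specialist autism school settings", a reader might infer that shared schools also inflate the standard error, or that trained staff dilute the comparison by a known amount. Neither is supported. Children are randomised individually, so a school effect common to both arms largely cancels (step 3). The article does not say how many children share a school, or that any school hosts both arms, so no contamination figure can be derived from it.

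**Conclusion.** The point holds for therapists, conditionally. The stated power is not an arithmetic error; it is correct for independent children, an assumption that the article does not state and that its one-arm therapist structure puts in doubt. If the therapist ICC is above zero, the stated power and any child-level interval are optimistic.

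Under the assumed 6 to 12 therapists and ICC of 0.01 to 0.05, the loss at an effect size of 0.28 runs from under 2 points to about 15 points (79.9% to 64.7%). The effect size detectable with 80% power rises from 0.280 to between 0.286 and 0.336. The size of the primary test would be about 5.5% to 10% where therapist effects vary around zero. The direction is secure; the amount cannot be fixed without the number of therapists and an ICC.

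**What to change.** 1. Record the treating therapist for each PACT-G child in the trial database.
2. In the SAP, allow for therapist clustering in the PACT-G arm only. Use either a partially nested mixed model (random therapist effect in that arm, small-sample degrees of freedom) or a bootstrap that resamples therapists in that arm and children in the TAU arm. State the resampling unit either way.
3. If the random effect is barely estimable within ADOS-module strata, which is plausible with few therapists, pre-specify the clustered analysis as a sensitivity analysis to the published model.
4. Restate power with the number of therapists and over a stated ICC range.

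The cost is SAP wording, one identifier, somewhat wider intervals and a slightly less favourable power statement. With few therapists, both methods estimate the therapist variance imprecisely, and the report should say so. No participants are added: recruitment closed on 30 April 2018, so the restated power serves interpretation and not design. Analysis waits for all 12-month outcomes, so the change can be made before the data are analysed.

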### Analysis plan

A statistical analysis plan will be written by the trial statisticians (AP and RE) and agreed by the trial principal investigators before submitting for approval by the Trial Steering Committee and Data Monitoring Committee before any analysis is undertaken. All statistical analyses will be carried out using the latest version of Stata [48] or MPlus [49].

In accordance with the Consolidated Standards of Reporting Trials (CONSORT) Statement for non-pharmacological interventions, we will report all participant flow. Descriptive statistics will summarise recruitment, drop-out and completeness of interventions. Analysis will be undertaken after all 12-month outcome measures are completed. The main efficacy analysis will follow intention-to-treat principles. For the primary outcome, baseline measurement will be complete, since required for randomisation. The proposed ANCOVA will provide estimates under an assumption of a missing-at-random (MAR) data mechanism. For secondary outcome measures the ANCOVA will be estimated using simultaneous equations for both baseline and follow-up measurements, including all participants with any pre- or post-randomisation measure under the MAR assumption. Where outcomes are unavailable on more than 10% of participants, a sensitivity analysis will be undertaken in which outcome scores will be multiply imputed using relevant available auxiliary baseline and follow-up measures and assuming the absence of a treatment effect. There will be no planned interim analysis for efficacy or futility. Summary statistics of baseline characteristics will be presented by randomised group without formal statistical tests.

#### Phase 1 – Efficacy analysis

We will test the primary hypothesis for between-group difference in the outcome ADOS total score using linear regression, stratified by ADOS module, covarying by baseline ADOS total score and dummy variables for site, gender and age group. Standard residual diagnostics will be applied and skew minimising transformations adopted where required. An overall effect size will be calculated pooling stratum specific estimates for strata defined by the ADOS module, weighted by their precision, using a 95% confidence interval estimated from 5000 bootstrap replicates.

The secondary outcomes will be analysed in a similar way but without stratification by ADOS module. A forest plot of effect sizes for primary and secondary outcomes will be presented. A test of homogeneity of effect size for the ADOS and BOSCC will be reported.

The primary paper will report a test of homogeneity of effect for the primary outcome in pre-school and school-age children. To be consistent with the treatment main effects analysis, the test of difference in treatment effect by age group will be based on the bootstrap *p* value over 5000 replicates of the pooled within-ADOS stratum estimate of the treatment difference. A secondary paper (see phase 3) will report an optimal moderation index [50] including bias correction from over-fitting to a finite sample.

#### Phase 2 – Mechanisms’ evaluation

Mediation analysis [15] gave detailed insight into an attenuated generalization in the original PACT trial across change in person, task and context (as above and Fig. 1). In the PACT-G trial we enhance generalisation *into home* by keeping parental dyadic cues constant, but increasing functionally relevant interaction contexts; and *into education* by enhancing relevant communication with education staff (LSA). The mechanism study will investigate the mediation process in this model and, through that, illuminate key basic knowledge about generalisation of acquired skills in autism. Some of the pathways of interest are illustrated in Fig. 3. If the efficacy analysis shows significant between-group differences in the mediators (DCMA and/or BOSCC at home (path a) and in education contexts (path c)), then we will use parametric regression models to:Test for mediation of the intervention on primary symptom outcome (ADOS) through DCMA and/or BOSCC at home (paths a,e,f)Test for mediation of the intervention on primary symptom outcome through DCMA and/or BOSCC in the education setting (paths c,d,f)Test for mediation of intervention on DCMA and/or BOSCC in education setting through DCMA and/or BOSCC at home (paths a,b,c)Use structural equation modeling to examine multiple pathways through DCMA and/or BOSCC at home and in the education setting to primary symptom outcome (paths a–f)

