## Abstract

**Background:**

Prior evidence shows that behaviours closely related to the intervention delivered for autism are amenable to change, but it is more difficult to generalise treatment effects beyond the intervention context. We test an early autism intervention designed to promote generalisation of therapy-acquired skills into home and school contexts to improve adaptive function and reduce symptoms. A detailed mechanism study will address the process of such generalisation. Objective 1 will be to test if the PACT-G intervention improves autism symptom outcome in the home and school context of the intervention as well as in the primary outcome research setting. Objective 2 will use the mechanism analysis to test for evidence of acquired skills from intervention generalizing across contexts and producing additive effects on primary outcome.

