## Methods/design

### Aims

The PACT-G study has two aims. Firstly, it will test whether the extended PACT-G social communication intervention protocol, using targeted enhancement strategies within home and education settings, improves transmission of treatment effect to:

(1) Researcher-assessed autism symptom outcome; (2) Autism symptoms and functional adaptation in home and education settings. This objective will be tested using blinded measures maximising the ability to detect meaningful change (see ‘Measures’ below) and evaluated by analysis at trial endpoint.

The second aim is a mechanism analysis that will use the experimental trial to illuminate core processes of generalisation of specific acquired competencies in autism across context: (1) We will build on the mediation analysis from our previous PACT Trial (see above) to test mediation of the generalised treatment effect in home and school, (2) We will test how effects in naturalistic contexts may combine to enhance transmission of effect to research-assessed symptoms in a standardised test setting. In doing this, we will use the pre-specified measures of mediation which were successful in our previous MRC PACT trial.

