**Fig. 3 Fig3:**
[figure not shown]
Key mediation pathways to be tested in the Paediatric Autism Communication Therapy-Generalised (PACT-G) Trial mechanism study

We will also repeat these four steps using researcher BOSCC as the outcome variable in place of the ADOS. Since all the measures are continuous, the indirect effects are calculated by multiplying relevant pathways and bootstrapping is used to produce valid standard errors for the indirect effects. All analyses will adjust for baseline measures of the mediators (BOSCC/DCMA), outcome (ADOS) and putative measured confounders. Mediation analyses are potentially biased by measurement error in mediators and hidden confounding between mediators and outcomes; we will build on our previous methodological and applied work in this context to include repeated measurement of mediators and outcomes to account for classical measurement error [15] and baseline confounding [51]. We will investigate the sensitivity of the estimates to these problems and that of unmeasured confounding using instrumental variable (IV) methods [52] with baseline covariate by randomization interactions as potential instruments [52].

Treatment compliance in the education setting is likely to be more variable than the high levels achieved with parents. We will estimate a complier average causal effect (CACE) estimate using instrumental variable methods, considering the extent of education-setting opt-in as a measure of compliance and randomisation as the instrumental variable.

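### The mediation analysis runs only if the mediators differ significantly between groups, so the indirect-effect part of Objective 2 may go unanswered and education-path estimates may be inflated by selection

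*Protocol article*

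**What the plan says.** In the protocol article, Phase 2 – Mechanisms' evaluation opens its list of analyses with a condition: "If the efficacy analysis shows significant between-group differences in the mediators". The mediators and settings are given as "DCMA and/or BOSCC at home (path a) and in education contexts (path c"). Four steps follow: mediation through the home measures, mediation through the education measures, mediation of the education measures by the home measures, and a structural equation model of all paths. The same four steps are then repeated with the researcher BOSCC as outcome.

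On inference, Phase 2 says that "the indirect effects are calculated by multiplying relevant pathways and bootstrapping is used to produce valid standard errors for the indirect effects". It does not mention the condition there.

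The objectives are stated without a condition. The abstract says: "Objective 2 will use the mechanism analysis to test for evidence of acquired skills from intervention generalizing across contexts and producing additive effects". The Aims section plans "to test mediation of the generalised treatment effect in home and school". Phase 3 plans moderation of paths a to f by age group, also without one. The article does not say what is done or reported if the condition fails.

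**The concern.** Three things follow from the rule as written.

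- **An unanswered aim.** Failing to reach significance on the treatment-mediator path is not evidence that nothing is mediated. If the condition fails, the plan gives no indirect-effect estimates, although they are the stated content of Objective 2.
- **Blocking across settings.** Read literally, the word joining home and education requires both. A miss in education would then also block step 1, the home pathway, which the article labels with paths a, e and f and which does not use path c. A setting-by-setting reading is also possible, and the text does not settle it.
- **Selection.** If an indirect effect is computed only when its first path is significant in the same data, that path's estimate is biased away from zero, and the product of paths inherits the bias. The bootstrap as described does not account for the selection.

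The education path is where this could matter. The article gives it no effect size and no power, and expects compliance in schools to vary more than among parents.

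**Working it through.** **Inputs from the article (Sample size calculations).** 110 followed up per group, alpha 0.05 for the power calculation, pre-post correlation r = 0.67. Earlier-trial effects: 1.22 on parental synchrony and 0.41 on child communication.

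**Assumptions, not in the article.** The condition is a two-sided test at 0.05 (it says only that differences are significant); one mediator per setting; mediator r of 0.50 to 0.67; education effects over a range.

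**Step 1: reproduce the stated power.** SE = √(1 − r²) × √(2/110). At r = 0.67 this is 0.7424 × 0.1348 = 0.100. Power is 79.9% at 0.28 and 90.9% at 0.33. The article states 80% and 90%, so the set-up matches.

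**Step 2: chance of passing, and bias given a pass.** Let d be the true effect and λ = d/SE. Then

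- P = Φ(λ − 1.96) + Φ(−λ − 1.96)
- mean estimate given a pass = d + SE × [φ(1.96 − λ) − φ(1.96 + λ)] / P

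For d = 0.20:

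- r = 0.67: SE = 0.100, P = 51.5%, mean given a pass 0.277, ratio 0.277/0.20 = 1.39.
- r = 0.50: SE = 0.117, P = 40.3%, mean given a pass 0.312, ratio 0.312/0.20 = 1.56.

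| True effect (SD) | Pass, r = 0.67 | Inflation | Pass, r = 0.50 | Inflation |
|---|---|---|---|---|
| 0.10 | 17% | 2.45 | 14% | 2.78 |
| 0.20 | 52% | 1.39 | 40% | 1.56 |
| 0.28 | 80% | 1.13 | 67% | 1.23 |
| 0.41 | 98% | 1.01 | 94% | 1.04 |
| 1.22 | about 100% | 1.00 | about 100% | 1.00 |

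Even at r = 0, inflation at 0.41 is 1.085, about 9%.

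**Step 3: does the indirect effect inherit it?** The product of paths was simulated at r = 0.67 with 20,000 trials per setting, a mediator-outcome coefficient of 0.3 (assumed) and no confounding.

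| Treatment-mediator effect | True indirect effect | Mean, no condition | Mean, given a pass | Ratio |
|---|---|---|---|---|
| 0.20 | 0.060 | 0.0598 | 0.0830 | 1.38 |
| 0.28 | 0.084 | 0.0842 | 0.0943 | 1.12 |
| 0.41 | 0.123 | 0.1233 | 0.1246 | 1.01 |
| 1.22 | 0.366 | 0.366 | 0.366 | 1.00 |

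The ratios match step 2. Without the condition the estimates are essentially unbiased.

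**Step 4: how loosely the condition is defined.** It allows DCMA, BOSCC or both. With two independent measures per setting and no effect on either, the chance that at least one passes is 1 − 0.95² = 9.75%. With a true effect of 0.20 on both, it is 1 − (1 − 0.403)² = 64% at r = 0.50 and 1 − (1 − 0.515)² = 76% at r = 0.67. The pass rate therefore depends on a reading that the text leaves open.

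**The case against.** Testing for an effect on the mediator before estimating mediation is a conventional sequence, and this is an explanatory analysis that leaves the primary efficacy result untouched. The rule also hides less than it first appears to. It depends on what the efficacy analysis shows, so the group differences in the mediators are estimated in any case. The abstract lists child interaction with parent or teacher among the secondary outcomes, and Phase 1 plans a forest plot of secondary effect sizes. The complier average causal effect for education-setting opt-in is not conditional either. All of this stands.

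A reader might infer three stronger things that the article does not support.

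- **That every reported indirect effect is inflated.** At the earlier trial's effects of 0.41 and 1.22 the inflation is 0% to 1% at r = 0.67.
- **That a weak school effect would go unreported.** The difference itself would be estimated. Only its decomposition into indirect effects would be withheld.
- **That both settings would pass together in only 38% to 51% of trials.** Those figures are 0.94 × 0.40 and 0.98 × 0.52. They need a home effect of 0.41, an education effect of 0.20, one measure per setting, independent tests and the both-settings reading. None of the last four is established. Two measures per setting, or positive correlation between home and school results, would raise the figure.

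The analysis plan is not at hand and may settle the wording. That does not remove the point, because the article itself states the data-dependent rule.

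**Conclusion.** The concern holds in a limited form. The article sets a significance condition on analyses that its objectives state unconditionally, and it offers no fallback. What can be lost is the indirect-effect part of Objective 2. On the literal both-settings reading, the home pathway can be lost through a miss in education.

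Selection bias is a conditional risk, chiefly on the education path. For an assumed true effect of 0.20 SD, one mediator per setting, a two-sided 5% test and r of 0.50 to 0.67, the condition passes in about 40% to 52% of trials and the path is overstated 1.6 to 1.4 times. At r = 0.67 the overstatement falls to 1.13 times at 0.28 and to about 1% at 0.41. The home path is essentially unaffected if effects resemble those of the earlier trial. The education effect, the mediator correlation and the test threshold are assumptions, because the article states none of them for the mediators.

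**What to change.** Delete the significance condition from Phase 2. State that paths a to f and all pre-specified indirect effects, for both the ADOS and the researcher BOSCC as outcome, will be estimated and reported with bootstrap 95% confidence intervals whatever the Phase 1 p-values.

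This costs one sentence and a little more analysis. The downside is that some indirect effects will be near zero with wide intervals, and the report should present them as imprecise.
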